## Abstract

Striae are common dermal lesions associated with physiological and psychological alterations, affecting the quality of life. This proposed randomized controlled trial protocol will evaluate the clinical efficacy and treatment safety of fractional CO_2_ laser versus fractional radiofrequency (FRF) in clinical trials. We will randomly allocate 60 subjects who present abdominal striae into two different groups for the treatment, which will be performed once a month for a 3-month period. The results will be assessed by quartile scoring criteria; by comparing digital photos taken before and after each treatment; and also, by the measurement of cutaneous temperature, skin pH, and elasticity before and after the treatment. This paper describes the rationale and the design of the randomized controlled trial, which may provide evidence for clinical application of the methodology and the quality related to the efficacy and safety of fractional CO_2_ laser versus the FRF protocol for striae treatment.

## 1. Introduction

Striae distensae (SD), also known as stretch marks, affect a large part of the world’s population and are becoming challenging to treat. In 1936, the first correct description of these lesions appeared, entitled as striae atrophicae [1]. Stretch marks are linear prevalent cutaneous lesions [2], characterized by epidermal atrophy [3]. The exact origin of this type of skin condition remains unclear; however, they occur mostly in some physiological and pathological situations, such as in adolescent growth, obesity, pregnancy, and topical steroid use [3,4]. Stretch marks appear at a higher frequency in pregnant woman and adolescents, in whom the prevalence ranges from 6 to 86% [5]. Lower back and knees are the most affected areas in males, while in women they mostly affect the calves, buttocks, and thighs [5].

Clinically, stretch marks are characterized by rapid elongation of the skin, which destroys the elastic fibers, affecting the dermis by decreasing the components of the extracellular matrix (ECM) such as collagen and elastin [5]. In the early stages, SD appear in a pink-red-purple color, with edematous scars called striae rubrae [5,6]. Over time, a decrease in vascularization is observed, with a degradation of collagen and elastin [5], which turns the striae into a white color with an atrophic look, known as striae albae [4,6]. Other different stria types have been identified such as striae caerulea and striae nigrae in individuals with darker skin, which are associated with an increase in their quantity of melanin [7]. Studies also demonstrate that different colors in stretch marks are influenced by melanocytes’ mechanobiology [8].

Despite being a physiological condition, striae still represent a disfiguring condition that creates a lot of psychological problems, affecting the quality of life of any individual with this pathology [9]. Many people look for therapies and treatments, and several have been proposed such as chemical peels, microdermabrasion, topical agents, and ablative and non-ablative energy devices [5]. However, the treatment of SD does not bring 100% effective outcomes since there is no consistent modality available [4]. In the late stages of striae, it becomes even more challenging to find a more effective treatment [2]. One of the modalities that is lately being used to upgrade and recover stretch marks is laser therapy [4], which represents an innovation in the approach to striae, particularly in striae rubrae [10], and is the most common therapeutic alternative recently [11]. Lasers should recover both striae depth and width as well as improve their histology, with an increase in the numbers of collagen and elastin fibers [12].

Skin lasers have improved, even more so after the development of fractional laser treatment, which is characterized by reepithelization due to the migration of viable cells from undamaged sites to the injury site [9]. Laser categories include non-ablative fractional laser, radiofrequency (RF), long pulsed Nd:YAG, fractional CO_2_ laser, fractional bipolar RF, fractional ablative microplasma RF, and intense pulsed light (IPL) [13,14]. Laser therapy represents a great advance in treating stretch marks, specifically striae rubrae, since there is an increase in the vascularization of the lesions [10].

Specifically, fractional CO_2_ laser treatment has been reported as a new resurfacing technique in SD treatments [9]. Here, fractional CO_2_ forms micro-thermal zones of damage, the necrotic debris is expelled, and neo-collagenesis occurs [15]. This technique stimulates epidermal turnover and dermal collagen remodeling, which leads to important improvements in texture and appearance in many types of scars, such as stretch marks [16]—mainly in mature striae [2]. After treatment with fractional CO_2_ laser, full recovery with normal epidermis, parallel arrangement of the collagen bands, and perivascular aggregation of inflammatory cells were demonstrated [16]. In phototype IV skin, the use of CO_2_ laser treatment has been discouraged on account of the high risk of pigmentary alteration [17], although theoretically, this type of laser stimulates fibroblast activity and improves lesions through controlled skin abrasion [18]. Regarding adverse effects, there are a few, and some are self-limiting, such as post-inflammatory hyperpigmentation; however, these effects can be fixed naturally in a few months after treatment [2].

Additionally, CO_2_ laser treatment is more painful and requires a longer recovery time [19] when compared with non-ablative lasers. Studies have shown a significant decrease in the strial surface area after resurfacing with fractional CO_2_ laser treatment when compared with topical therapy (10% glycolic acid + 0.05% tretinoin) [20]. Lee et al. also demonstrated that fractional CO_2_ laser treatment, specifically at 10,600 nm, had a positive effect on late-stage SD, with clinical improvement with only one session [21]. When used in striae albae, fractional CO_2_ laser treatment was shown to be effective in subjects with skin types III and IV [20], and another study also demonstrated that two out of five patients with striae albae showed changes after 4-week treatment intervals with fractional CO_2_ laser [22].

Concerning RF, this type of technique provides different patterns of heat distribution [23]. Unlike lasers, which convert light to heat and focus on specific chromophores, RF devices transfer a high-frequency alternating electrical current that goes through the dermis and hypodermal tissues without affecting the epidermal–dermal barrier [2]. That electrical current is converted into heat, mediating thermal damage to the surrounding connective tissue responsible for denaturing elastic fibers and collagen [24], which occurs immediately after RF treatment [4]. This collagen denaturation represents the tissue contraction, which induces inflammation and stimulates fibroblasts to produce new collagen, new elastin, and ground substances [3]. These alterations intensify the dermal tissue and help to improve the appearance of striae due to the increased production of collagen and elastin [3,24]. Regarding bipolar RF, it has shown clinical and histological improvements in striae distensae, while tripolar RF resulted in a 25–75% improvement in just one week of treatment [25]. Overall, RF is associated with an increase in the production of the dermis, improving SD [26]. A study showed that 14 of 16 subjects observed visible changes, with statistically significant reductions in both the length and width of striae bands [3]. To improve the tissue heating patters, fractional radiofrequency (FRF) was developed, which induces dermal heating [23]. FRF is safe for all skin types due to its “colorblind” nature, being applied directly to the skin surface or within the skin [23]. Even though the side effects were mild and transient, pain remains a significant limitation to the use of FRF, specifically in sensitive body areas such as the abdomen [27].

Overall, only a limited number of studies have been conducted that investigated the effectiveness of different types of treatments for stretch marks, specifically comparing two different types of treatment. Taking that into account and considering the characteristics of both fractional CO_2_ laser and fractional radiofrequency, we would like to focus this work on the evaluation and comparison of the clinical efficacy and treatment safety of both techniques in clinical applications (STRIAL). To evaluate the impact of stretch marks reduction on the quality of life and on body image, two hypotheses are proposed: the clinical efficacy and safety of fractional CO_2_ laser are superior to fractional radiofrequency, or the clinical efficacy and safety of fractional radiofrequency are superior to the fractional CO_2_ laser.

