## 2. Materials and Methods

### 2.1. Study Design

We propose a randomized controlled trial, 1 to 1, that aims to compare the clinic efficacy and safety of two different treatments for striae: fractional CO_2_ laser treatment versus fractional radiofrequency (FRF). This trial will be conducted according to the trial procedure presented in the flowchart in Figure 1.

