### 2.3. Eligibility Criteria

Inclusion and exclusion criteria will be applied in the participant selection process. This trial will include male and female patients who are aged 18 years or older and have stretch marks, only in the abdomen area. Patients that refuse to participate in the study; who have a history of keloids, skin infections, or connective tissue disease; or are pregnant will be excluded. Other cases such as participants who take vitamin A and derivatives within two months of the beginning of the study and the use of immunosuppressive drugs will be also excluded from the study.

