### 2.4. Allocation

After screening for eligibility and explaining the objectives and procedures for the research project implementation, written informed consent will be obtained from each individual who agrees to participate. In addition, an individual evaluation will be performed regarding the clinical history and the actual striae. Thirty participants will randomly be assigned each to Group A (CO_2_ laser) and Group B (FRF) following a simple randomization procedure involving random selection from two envelopes, each of which will indicate the type of stria treatment.

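### The article reports a phototype-specific pigment risk for CO2 laser, but a trial that compares safety allocates 60 people without stratifying by phototype

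*Protocol article*

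**What the plan says.** **Risk by skin type.** The Introduction states: "In phototype IV skin, the use of CO_2_ laser treatment has been discouraged on account of the high risk of pigmentary alteration". That sentence does not say whether it concerns fractional devices. The same section reports that fractional CO2 laser was effective in striae albae in skin types III and IV, and says of adverse effects that "some are self-limiting, such as post-inflammatory hyperpigmentation". Of the comparator it says: "FRF is safe for all skin types due to its “colorblind” nature".

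**Aim and population.** Section 2.1 describes a 1:1 trial that "aims to compare the clinic efficacy and safety of two different treatments for striae". Section 2.3 admits "male and female patients who are aged 18 years or older and have stretch marks, only in the abdomen area". Its exclusions include people "who have a history of keloids, skin infections, or connective tissue disease; or are pregnant will be excluded", and no criterion mentions phototype. The Discussion gives, as one reason for a sample of 60, a better chance of including different types of skin.

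**Allocation.** Before allocation, section 2.4 says that "an individual evaluation will be performed regarding the clinical history and the actual striae". Thirty people are then assigned to each group by "a simple randomization procedure involving random selection from two envelopes". Table 1 lists clinical data, a physical examination and randomisation.

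**Safety outcome.** Section 3.4 names hyperpigmentation and hypopigmentation among the reactions to be reported and managed.

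**The concern.** Phototype is a baseline characteristic for which the article itself reports a safety concern with one treatment and not with the other. Two consequences follow for the comparison of pigment events.

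- **Chance imbalance.** With 60 people and no stratification, the arms may differ in the share at higher pigmentary risk. Part of an observed difference in pigment events could then reflect who was in each arm.
- **Dependence on the mix.** If the excess risk belongs to CO2 laser in darker skin, the overall difference between arms depends on how many such people enrol. A pooled figure from a mainly light-skinned sample could understate the risk in phototype IV.

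The allocation method is stated outright in section 2.4, so the point concerns what the article specifies and not a detail left to a longer document.

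**Working it through.** The article gives no figure to reproduce here: it states neither a phototype share nor a pigment-event rate. The calculations below size the issue under labelled assumptions.

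**Inputs from the article:** 60 people, 30 per arm (section 2.2); simple unstratified allocation (section 2.4).

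**Assumed inputs:** the share with phototype IV or darker is 10%, 20%, 30% or 40%, that is K = 6, 12, 18 or 24 people. Grouping darker types with IV is also an assumption, since the Introduction's caution names type IV only.

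**1. Chance imbalance.** With arms fixed at 30/30, the number X of such people in the CO2 arm is hypergeometric (60, K, 30). The difference in share between arms is |2X − K|/30, so 20 points means 6 people. With coin-toss allocation, realised arm sizes are used.

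| Assumed share | Expected in CO2 arm | P(≥20 points), 30/30 | P(>20 points), 30/30 | P(≥20 points), coin toss |
|---|---|---|---|---|
| 10% | 3 | 2.4% | 0% | 0.9% |
| 20% | 6 | 10.4% | 2.1% | 6.1% |
| 30% | 9 | 15.8% | 4.7% | 10.0% |
| 40% | 12 | 18.7% | 6.4% | 12.9% |

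Much of the probability in the 30/30 column sits exactly at 20 points. The standard deviation of the signed difference in share, with 30/30 fixed, is 7.8, 10.4, 11.9 and 12.8 points.

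**2. Effect of a 20-point imbalance.** Assume that pigment events occur in 10% of lighter skin and in 30% (or 50%) of phototype IV and above, equally in both arms.
- Shift in the arm difference: 0.20 × (0.30 − 0.10) = 0.04, or 0.20 × (0.50 − 0.10) = 0.08.
- Overall event rate p = 0.10 + share × 0.20 (or × 0.40), which runs from 0.12 to 0.26.
- Standard error = √(2p(1 − p)/30), which runs from 0.084 to 0.113.

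The shift of 4 or 8 points is below one standard error in every case.

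**3. Dependence on the mix.** Assume instead that only CO2 laser carries the excess and that FRF stays at 10%.
- With 30% in IV and above: share × 0.20 = 2, 4, 6 or 8 points overall, although the difference within phototype IV and above is 20 points.
- With 50%: share × 0.40 = 4, 8, 12 or 16 points overall, against 40 points within that group.
- Standard error of the overall difference: 0.081 to 0.097.

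The pooled figure thus varies with enrolment and is always smaller than the difference in the group at risk.

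**4. What stratified blocks achieve.** With blocks of 4 in two strata, an incomplete block can leave at most 2 more people in one arm within a stratum. The largest difference in share is 2/30 = 6.7 points. If both strata end off balance in the same direction, the arm totals are 32/28.

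**5. What they do not achieve.** Cells stay small. With zero events among n people, the one-sided 95% upper limit is 1 − 0.05^(1/n): 63%, 39%, 28% and 22% for n = 3, 6, 9 and 12.

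**The case against.** The case against has several sound parts.

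- **Unstratified randomisation is valid.** It balances phototype in expectation, and stratifying 60 people on a factor that may have only 6 in one level is a design preference. This stands: there is no bias and no error of randomisation.
- **The effect is small and rests on assumed rates.** This stands too, as step 2 shows. Stratifying also leaves the enrolled mix unchanged, so step 3 supports reporting by phototype and not the stratification itself.
- **The premise is softer than it looks.** The caution does not specify fractional devices and names type IV only. The same section reports efficacy in types III and IV and calls hyperpigmentation self-limiting. All of this limits the weight of the point. However, efficacy does not answer a pigment-safety warning, and the self-limiting remark does not mention hypopigmentation, which section 3.4 also lists.
- **Phototype may be recorded anyway.** The baseline evaluation or physical examination could include it; the article neither confirms nor excludes this. Recording alone would not alter the stated draw.

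A reader might go further and infer that the plan contradicts itself, or that it exposes phototype IV to CO2 laser without protection because section 2.5 gives one pulse power of 100 W and adapts only the tip, to lesion width. The document does not support either inference. Reporting a concern and then comparing safety across varied skin, with pigment changes monitored, is coherent. Section 2.5 says that laser absorption depends on skin properties, and it states no pulse duration, energy or coverage, so 100 W alone does not establish a fixed delivered dose. Settings and precautions by phototype may well be in the full protocol.

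**Conclusion.** The point holds as a modest issue of precision and of safety interpretation. The article reports a risk factor specific to one treatment, makes safety a stated comparison, welcomes varied skin, and specifies an allocation method that leaves the balance of that factor to chance. For assumed shares of 10% to 40%, an imbalance of at least 20 points has a 2% to 19% chance with 30/30 fixed (1% to 13% with coin-toss allocation), and under the assumed rates it would move the arm difference by less than one standard error.

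The interpretive part needs no imbalance: if only CO2 laser carries the excess, the pooled difference depends on the enrolled mix and should not be applied to phototype IV.

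The shares, the event rates and the grouping of IV with darker types are all assumptions. Confidence is medium, mainly because the article does not settle whether the reported caution covers fractional devices.

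**What to change.** - Record Fitzpatrick phototype at the baseline physical examination, before allocation.
- Replace the two-envelope draw with concealed blocked allocation in two strata, I–III versus IV and above.
- Report hyperpigmentation and hypopigmentation descriptively by arm and phototype level, without a subgroup test, and extend no safety conclusion to phototype IV from the pooled figure alone.

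The cost is one baseline field, a second allocation list, one extra step at randomisation and a short amendment. With blocks of 4, arm totals may end as far apart as 32/28. The phototype cells stay small, because stratification balances them without enlarging them. The change makes the safety comparison easier to read; it does not by itself reduce the pigmentary risk to anyone assigned to CO2 laser.

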## 2. Materials and Methods

### 2.1. Study Design

We propose a randomized controlled trial, 1 to 1, that aims to compare the clinic efficacy and safety of two different treatments for striae: fractional CO_2_ laser treatment versus fractional radiofrequency (FRF). This trial will be conducted according to the trial procedure presented in the flowchart in Figure 1.

### 2.3. Eligibility Criteria

Inclusion and exclusion criteria will be applied in the participant selection process. This trial will include male and female patients who are aged 18 years or older and have stretch marks, only in the abdomen area. Patients that refuse to participate in the study; who have a history of keloids, skin infections, or connective tissue disease; or are pregnant will be excluded. Other cases such as participants who take vitamin A and derivatives within two months of the beginning of the study and the use of immunosuppressive drugs will be also excluded from the study.

### 2.4. Allocation

After screening for eligibility and explaining the objectives and procedures for the research project implementation, written informed consent will be obtained from each individual who agrees to participate. In addition, an individual evaluation will be performed regarding the clinical history and the actual striae. Thirty participants will randomly be assigned each to Group A (CO_2_ laser) and Group B (FRF) following a simple randomization procedure involving random selection from two envelopes, each of which will indicate the type of stria treatment.

### 2.5. Intervention

Regarding the clinical procedures, the CO_2_ laser (CO_2_RE^®^, Candela, Marlborough, MA, USA) group will undergo three sessions, once a month over 3 months. The laser procedure has the following indications: laser tip diameter from 1 to 10 millimeters (mm), according to the width of the lesions; pulse power of 100 W; and repetition rate of 20 Hz using a single pass. During this procedure, a cryotherapy advice (Cryo 6, Zimmer, Germany) will be applied to reduce any pain. Since laser absorption is related to skin properties [28], there is a need to have both the reflectance and absorbance spectra of human skin. This is the key to quantitatively and non-invasively analyzing skin components. Figure 2 represents the relative penetration of different wavelength in all skin layers. Figure 3 represents a hyperspectral skin image, with the reflectance of different wavelength in the visible light range.

The FRF group will also undergo three sessions, once a month over 3 months. The procedure of this treatment will be performed with a set of 24 RF conductive needles. Each needle has a length of 2500 micrometers (μm). Patients will receive initial doses of 20–40 mJ/pin, and the doses will be increased at each session based on patient tolerance. All treated areas will receive a pass based on the treatment site and patient tolerance. During this procedure, cryotherapy will be applied with a Zimmer G system to reduce the patient’s pain.

For clinical improvement, before and after photos of an individual that went through laser CO_2_ treatment for abdominal striae will be used as a control (Figure 4); high-resolution digital photographs will be taken before and after both treatments at every session, starting at the baseline. Two physicians blinded to the study will compare these photographs using quartile scoring criteria for the assessment (0 = no improvement; 1 = mild (25% improvement); 2 = moderate (>25 ≤ 50% improvement); 3 = good (>50 ≤ 75% improvement); 4 = excellent (≥76% improvement)).

Additionally, measurements of cutaneous temperature, pH, and skin elasticity will be taken at the baseline and before and after each treatment. Cutaneous temperature will be measured by a thermograph (FLIR i7), positioned at 7 cm away from the abdomen area. The skin pH will be measured by pH bands. The skin elasticity will be measured by an elastometer.

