## 3. Results

### 3.1. Primary Outcome

The primary outcome measure will focus on the change in the quartile scoring criteria by comparing the digital photos taken before and after each treatment (fractional CO_2_ laser and FRF) for clinical improvements in the affected area (abdomen). This process will be assessed by two physicians blinded to the study. Figure 4 will be the control, being compared to the pictures taken during the study.

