**Figure 4 healthcare-10-02372-f004:**
[figure not shown]
Before (**A**) and after (**B**) control photos of abdominal striae of an individual subjected to laser CO_2_ treatment.

**Table 1 healthcare-10-02372-t001:** Timing of visits and data collection, according to the Standard Protocol Items: Recommendations for Interventional Trials (SPIRIT).

				Treatment Period		
		Screening	Baseline 0-Month	1-Month	2-Month	3-Month
Patient	Eligibility Informed consent Clinical data Physical examination Randomization	X	X X X X			
Intervention	Fractional CO_2_ laser: Group A			1 session per month for 3 months		
	Fractional radiofrequency: Group B			1 session per month for 3 months		
Outcomes	Digital photo collection		X	X	X	X
	Cutaneous temperature		X	X	X	X
	Skin pH		X	X	X	X
	Skin elasticity		X	X	X	X
Participant Safety	Adverse effects			X	X	X

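### The primary score draws on photographs taken after each session with no restriction to recovered skin, so treatment marks can break reader blinding and distort the improvement grade

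*Protocol article*

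**What the plan says.** Section 2.5 (Intervention) of the protocol article sets the photograph rule: "high-resolution digital photographs will be taken before and after both treatments at every session, starting at the baseline". The next sentence gives the reading rule: "Two physicians blinded to the study will compare these photographs using quartile scoring criteria for the assessment". The score runs from 0 (no improvement) to 4 (excellent).

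Section 3.1 (Primary Outcome) bases the primary outcome on "comparing the digital photos taken before and after each treatment (fractional CO_2_ laser and FRF) for clinical improvements", and adds: "This process will be assessed by two physicians blinded to the study". Section 2.5 also supplies a reference for the readers: "before and after photos of an individual that went through laser CO_2_ treatment for abdominal striae will be used as a control".

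On what the devices do to skin, the Introduction says that "fractional CO_2_ forms micro-thermal zones of damage, the necrotic debris is expelled", and section 2.5 says of radiofrequency: "The procedure of this treatment will be performed with a set of 24 RF conductive needles". Section 3.4 lists erythema, edema, irritation and pigment change among the expected reactions, without separating the arms.

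Table 1 marks one photograph collection at each of baseline and months 1, 2 and 3. It does not divide any visit into a pre-session and a post-session image.

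**The concern.** The primary outcome is a subjective judgement of percent improvement, and reader blinding is the only masking the article describes. That blinding works only if the images do not show which device was used. The reading rule takes in the whole set of session photographs, including those taken after treatment, and this puts two things at risk.

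- **Unmasking.** One arm receives ablative micro-thermal injury and the other a needle array. If the fresh marks look different, a physician viewing a high-resolution image may infer the arm. Any prior view about laser versus radiofrequency can then enter the score, and no analysis can take it out.
- **Distorted grading.** Redness and swelling soon after a session can hide or exaggerate striae. The grade would then partly reflect acute reaction instead of improvement, even with perfect masking. If the reaction differs between arms, so does the distortion.

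The reference case adds to the first risk: it comes from the CO2 laser arm and gives the readers a template for one of the two treatments.

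**Working it through.** **1. Which images are scored.** In section 2.5 the reading sentence follows the photograph sentence directly and refers back to it. Its only antecedent is the full set: before and after, at every session. Section 3.1 repeats the before/after comparison as the primary outcome. No section excludes post-session images or sets an interval since treatment. With three sessions and one image before and one after each, that is 3 × 2 = 6 session images per participant, of which 3 are post-session.

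**2. Whether those images could show the arm.** The article describes two different injuries (Introduction; section 2.5), a laser tip of 1 to 10 mm matched to lesion width against 24 needles each 2500 μm long (section 2.5), and expected erythema and edema (section 3.4). A visible difference in photographs is a reasonable inference from these passages. The article does not state it.

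**3. What remains if post-session images are left out.** The answer depends on when the sessions fall, and the article can be read two ways.

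| Reading | Sessions at month | Latest image not taken just after a session | Sessions it reflects |
|---|---|---|---|
| Table 1 places the sessions under months 1 to 3 | 1, 2, 3 | Month 3, pre-session | 2 of 3 |
| Section 2.5 starts the session photographs at baseline | 0, 1, 2 | Month 3 | 3 of 3 |

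Table 1 schedules no photograph after month 3.

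**4. Illustration of size.** The plan gives no SD, effect size or power figure, so there is nothing of its own to reproduce.

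- From the documents: 30 per arm (section 2.2) and a 0.05 significance level (section 3.5).
- Assumed: two-sided testing; score SD 0.8, 1.0 or 1.2; no true difference; a reader lean b of 0.25 or 0.5 point towards one arm, carried in full into the difference between arm means.
- SE = SD × √(2/30), which gives 0.207, 0.258 and 0.310.
- Rejection probability = Φ(b/SE − 1.96) + Φ(−b/SE − 1.96).

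| SD | b = 0.25 | b = 0.5 |
|---|---|---|
| 0.8 | 0.227 | 0.677 |
| 1.0 | 0.162 | 0.491 |
| 1.2 | 0.127 | 0.365 |

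For example, with SD 0.8 and b = 0.25, b/SE = 0.25/0.207 = 1.21 and Φ(1.21 − 1.96) ≈ 0.227. A t test with 58 degrees of freedom gives nearly the same: 0.125–0.222 for 0.25 point and 0.355–0.663 for 0.5 point.

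**The case against.** A reader might infer that the two physicians are simply not blind. The documents do not support that. Sections 2.5 and 3.1 both call them blinded, and what follows from the image rule is that blinding can be broken, not that it has been.

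Nor does the article say that photographs are taken immediately after treatment. That is the natural reading of a rule tied to every session, but no interval is written. Table 1 shows only "Digital photo collection X X X X", one mark per visit. Section 3.1 names the two modalities in parentheses after the word treatment, so its comparison could mean before and after a whole course. These points make the scored set ambiguous. They do not remove post-session images from it, because section 2.5 ties the photographs to each session.

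Recognisable device marks are likewise inferred. The Introduction describes a tissue mechanism and section 2.5 a needle count; neither describes an appearance. The reactions in section 3.4 are not assigned to an arm, so they do not identify it. They can still distort the grade.

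The error rates do not measure this defect. SD and lean are assumed, and nothing in the article links the lean to how often readers would recognise the arm.

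Coding, shuffling and relabelling images are details that a journal article may leave to the full protocol, so their absence is no finding. What stands is narrower: the article itself states which images are scored, and states it badly.

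**Conclusion.** The point holds as a badly fixed rule for the primary outcome. Read plainly, sections 2.5 and 3.1 send photographs of recently treated skin to the readers. The stated blinding is therefore exposed to treatment marks, and the grade to transient erythema or edema. The second problem does not depend on readers recognising the arm.

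The conclusion rests on two inferences: that a photograph taken after treatment at a session shows skin that has not yet recovered, and, for unmasking, that the two devices leave visibly different marks. Both are plausible; neither is written. The size of the bias cannot be derived from the documents. The illustrative ranges of about 13–23% and 37–68% show only that, with 30 per arm, a lean well under one score point would matter. The rule should be settled before any image is read, since a reader who has seen such images cannot be blinded again.

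**What to change.** State in sections 2.5 and 3.1 that the primary score compares baseline with later images of recovered skin only: the pre-session images at later visits, and the last scheduled image if it is not taken just after a session. Give these images to the readers coded and in random order. Keep post-session images for the safety record. Asking each reader to guess the arm after scoring is an inexpensive addition that would let the success of blinding be reported.

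Reconcile the session and photograph timing in section 2.5 and Table 1, and say which sessions the primary score covers.

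**Cost.** The selection rule uses photographs already planned, but it has a price. Post-session images no longer feed efficacy. If the third session falls at month 3, the last usable image in Table 1 reflects only two of the three sessions; covering the full course would then need a later photograph that Table 1 does not schedule. If the sessions end before month 3, the month 3 image covers all three.

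**Limit.** The fix lowers the risk without removing it. Section 3.4 lists pigment change, and the Introduction says that hyperpigmentation after CO2 laser can take a few months to resolve, so some pre-session images may still carry marks.
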